**Figure 1. F1:**
[figure not shown]
Flowchart of the study design showing participant screening, randomization, allocation to the intervention group (lymphovenous bypass [LVB]+standard of care [SOC]) or the control group (SOC alone), follow-up assessments, and outcome analysis in participants with diabetic peripheral neuropathy (DPN). Outcome assessors and statisticians remain blinded to group allocation. ABI: ankle-brachial index; BUN: blood urea nitrogen; DN4: Douleur Neuropathique 4; Glu AC: glucose *ante cibum*; HbA_1c_: hemoglobin A_1c_; HRV: heart rate variability; IENFD: intraepidermal nerve fiber density; MNSI: Michigan Neuropathy Screening Instrument; QST: quantitative sensory testing.

**Table 1. T1:** SPIRIT (Standard Protocol Items: Recommendations for Interventional Trials)–aligned trial progression, including screening, baseline evaluation, surgical intervention, and longitudinal assessment of study end points.

Trial procedures	Enrollment (month −1)	Baseline (month 0)	Intervention (day 0)	First follow-up (month 6)	Second follow-up (month 12)
Enrollment					
Eligibility screening	✓				
Informed consent	✓				
Randomization		✓			
Interventions					
Lymphovenous bypass+SOC^a^ (experimental)			✓		
SOC alone (control)			✓		
Assessments					
Medical history and BMI		✓			
Laboratory tests (eg, hemoglobin A_1c_)		✓			
*Douleur Neuropathique* 4 questionnaire (neuropathic pain)		✓		✓	✓
Michigan Neuropathy Screening Instrument (diabetic peripheral neuropathy burden)		✓		✓	✓
Sudoscan (electrochemical skin conductance)		✓		✓	✓
Nerve conduction studies–electromyography		✓			
Heart rate variability and quantitative sensory testing		✓		✓	✓
Ulcer photography and ulcer status assessment		✓		✓	✓
Skin biopsy (intraepidermal nerve fiber density)		✓			✓
Biomarkers (oxidative stress)		✓		✓	✓
Adverse event and safety monitoring			✓	✓	✓

a SOC: standard of care.

### Intervention

#### Experimental Intervention (LVB+SOC)

Participants allocated to the experimental arm will undergo LVB in addition to SOC. This SOC consists of guideline-based glycemic and cardiovascular risk-factor management, neuropathic pain control, footwear or offloading, and standardized wound care for participants with ulcers. Routine SOC outpatient visits (eg, routine diabetes and wound clinic appointments at standard intervals) will occur according to standard clinical practice guidelines. Lymphatic mapping will be performed with intradermal blue dye injection, followed by a 2 to 3 cm dorsal foot incision and supermicrosurgical lymphatic-venous anastomosis (end-to-end or end-to-side) to adjacent venules ≤0.8 mm in diameter under microscopy, using 11-0 or 12-0 nylon sutures. At least 1 anastomosis will be completed according to anatomical and flow characteristics, with minimal expected blood loss (<5 mL). In participants with ulcers, concomitant debridement with or without grafting will be undertaken according to IWGDF-IDSA guidelines, followed by standardized postoperative wound care and offloading. Postoperative management will include 24 hours of limb elevation, early mobilization, standard analgesia, and antibiotics if grafting is performed. Treatment fidelity will be maintained by a single credentialed plastic microsurgeon following standardized operating procedures, with intraoperative documentation of the number and type of anastomoses, venous backflow, and confirmation of dye transit.

#### Control Intervention (SOC Alone)

Participants assigned to the control arm will receive SOC only, consisting of guideline-based glycemic and cardiovascular risk-factor management, neuropathic pain control, footwear or offloading, and standardized wound care for those with ulcers. No sham procedure will be performed owing to ethical considerations.

### Outcomes

The primary objective is to compare LVB+SOC with SOC alone in terms of changes in neuropathic pain, assessed by the DN4 questionnaire, and DPN burden, measured by the MNSI at 6 and 12 months. Secondary objectives are to evaluate sudomotor function using Sudoscan, large-fiber nerve conduction parameters, and, in participants with ulcers, time to complete epithelialization adjudicated by blinded review, the proportion of ulcers healed by 20 weeks, infection episodes, reoperations, and rates of minor or major amputation. Exploratory objectives include assessment of serum oxidative stress and antioxidant indices, inflammatory cytokine profiles, and IENFD. The safety objective is to characterize adverse events, serious adverse events, surgical site complications, and hypersensitivity reactions to intraoperative mapping dyes [24].

### Schedule of Assessments

#### Baseline Assessments

At trial inclusion, demographic and clinical variables will be collected, including age, sex, and relevant past medical history (including diabetes mellitus, hypertension, chronic kidney disease, and diabetic retinopathy) from the electronic medical record. Physical examination parameters will include BMI and waist circumference. Laboratory assessments will comprise fasting plasma glucose, glycated hemoglobin (hemoglobin A_1c_), triglycerides, blood urea nitrogen, and serum creatinine. Baseline severity of diabetic neuropathy will be evaluated through NCS, QST, HRV, ESC (measured using Sudoscan, if not performed within the preceding 3 months), and symptom scoring with the MNSI and DN4. Ulcer status will be documented and photographed when present, and IENFD from ulcer biopsy specimens will be evaluated by a neurologist.

#### Follow-Up Assessments

At 6 months, participants will undergo repeat assessments, including Sudoscan, HRV, QST, MNSI, and DN4, with testing supported by self-payment arrangements. Additionally, any changes in time-varying covariates, such as concomitant treatments (eg, adjustments to neuropathic pain medications or glycemic control agents), will be systematically reviewed and recorded. At 12 months, similar assessments (Sudoscan, HRV, QST, MNSI, and DN4) and IENFD evaluation will be performed, with reimbursement provided under the National Health Insurance framework. These follow-up evaluations are intended to capture both the primary end point at 6 months and the durability of outcomes at 12 months.

### Statistical Analysis

A total sample size of 60 randomized participants (LVB n=40; SOC n=20) provides 80% power (*α*=0.05) to detect a conservative between-group effect size of Cohen *d*=0.70 for the primary end point. This target randomized sample size accounts for an anticipated 15% dropout and missing data rate across both groups to ensure that the study remains adequately powered for the final analysis. This calculation was performed using G*Power (version 3.1.9.7) based on a 2-sample *t* test framework to ensure robust power for the subsequent longitudinal analysis. All statistical analyses will be performed using SPSS (version 28.0; IBM Corp). The primary analysis will follow the intention-to-treat principle, with per-protocol analyses conducted as sensitivity checks. The primary end point—jointly defined as the changes in DN4 and MNSI at 6 and 12 months—will be analyzed using a mixed-effects model for repeated measures (MMRM). Continuous secondary end points, including ESC values, SSR latencies or amplitudes, HRV parameters, and QST thresholds, will be analyzed using identical, parallel MMRM frameworks to control for baseline values and time-varying covariates. Exploratory biomarker analyses will use analysis of covariance or mixed models, with multiple testing controlled by the Benjamini-Hochberg false discovery rate. Missing data will be assumed to be missing at random, with MMRM inherently accommodating missingness and multiple imputation using Multiple Imputation by Chained Equations applied for sensitivity analyses. To ensure stability, given the small control group (n=20), Multiple Imputation by Chained Equations will use a restricted set of covariates. An anticipated dropout and missing data rate of 15% is expected across both groups. Prespecified exploratory, hypothesis-generating subgroup analyses will evaluate outcomes by ulcer status, baseline DPN stage, hemoglobin A_1c_ tertiles, dyslipidemia, and chronic kidney disease. Interim analyses will be restricted to safety reviews by the DSMB after approximately 20 and 40 participants, with no efficacy-based stopping rules.

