**Methods:**

This is a SPIRIT (Standard Protocol Items: Recommendations for Interventional Trials)–aligned, single-center, randomized, controlled, parallel-group superiority trial with a 2:1 allocation (LVB+SOC vs SOC alone). Randomization is stratified based on the presence or absence of active diabetic foot ulcers, as defined by the International Working Group on the Diabetic Foot and Infectious Diseases Society of America criteria. In total, 60 adults aged 20 to 80 years with confirmed DPN will be enrolled. LVB involves lymphatic-venous anastomosis to venules ≤0.8 mm. SOC consists of guideline-based glycemic and risk-factor management, pain control, and standardized wound care. Outcome assessors and statisticians are blinded. The primary outcomes are changes in clinical neuropathy burden and pain severity at 6 and 12 months. Secondary outcomes comprise objective measures of somatic and autonomic physiology, histopathological nerve fiber density, biological serum markers, and longitudinal ulcer epithelialization parameters. Data analysis will use mixed-effects models for repeated measures, with a sample size of 60 adults providing 80% power to detect a conservative between-group effect size of Cohen *d*=0.70.

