## Methods

### Design and Setting

This study is a SPIRIT (Standard Protocol Items: Recommendations for Interventional Trials)–compliant, single-center, randomized, controlled, parallel-group superiority trial with a 2:1 allocation ratio (LVB+SOC vs SOC alone). Participants will be stratified based on whether they have an active diabetic foot ulcer—explicitly classified as Wagner Grade ≤2 according to International Working Group on the Diabetic Foot (IWGDF) and Infectious Diseases Society of America (IDSA) criteria—or do not have an active ulcer at the time of enrollment. This uneven allocation maximizes exposure to the novel LVB intervention, prioritizing robust safety and efficacy data for the experimental arm while maintaining a valid and adequately powered control group. Outcome assessors, including Sudoscan and NCS technicians, as well as statisticians will remain blinded to group assignment. The trial will be conducted within the National Taiwan University Hospital system, encompassing both outpatient and inpatient wound care and diabetes clinics.

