Several limitations must be acknowledged. The single-center design may constrain generalizability, and the inability to blind participants and surgeons introduces a risk of performance bias, although this limitation is mitigated by the use of objective, assessor-blinded measures such as ESC and NCS. The heterogeneity of DPN phenotypes, including the broad age range (20-80 years) included in our eligibility criteria, presents additional challenges in interpreting subgroup responses; however, our statistical model adjusts for age and diabetes duration to mitigate this issue. Although the sample size is adequately powered for the primary end point, it may be underpowered to detect smaller effects across secondary and exploratory outcomes. The small sample size, particularly in the SOC control group (n=20), poses a significant constraint relative to the planned complex multivariable MMRM analyses and increases the risk of unstable estimates. Future research should include multicenter replication to validate findings, cost-effectiveness analyses to assess feasibility in routine practice, and refinement of indications such as early autonomic DPN or refractory ulcer phenotypes. Comparative effectiveness studies, including evaluation alongside emerging pharmacologic agents such as glucagon-like peptide-1 receptor agonists, are also warranted. Taken together, this trial has the potential to establish LVB as a paradigm-shifting intervention that redefines the therapeutic landscape of DPN.

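### The stated 80% power for d=0.70 with 40 versus 20 participants does not reproduce: a two-sided t test gives 71% with no losses and 64% after the planned 15% dropout

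*Protocol article*

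**What the plan says.** The Statistical Analysis section gives the sample size justification in full apart from one input:

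- Size and power: "A total sample size of 60 randomized participants (LVB n=40; SOC n=20) provides 80% power", with alpha 0.05 and Cohen d=0.70 for the primary end point.
- Losses: the target of 60 "accounts for an anticipated 15% dropout and missing data rate across both groups".
- Method: G*Power 3.1.9.7, two-sample t test.
- Number of sides: not stated here or anywhere else in the article.

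The Abstract repeats the claim: "with a sample size of 60 adults providing 80% power to detect a conservative between-group effect size" of d=0.70. Two other places rely on it without giving a figure. Design and Setting justifies the 2:1 allocation as maximising exposure to LVB "while maintaining a valid and adequately powered control group". The limitations paragraph of the Discussion opens a sentence with "Although the sample size is adequately powered for the primary end point" and confines its warning about low power to smaller effects on the secondary and exploratory outcomes.

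**The concern.** A 2:1 split is less efficient than an equal one, and 20 controls is few for a standardised difference of 0.70. Reaching 80% power with that split, with room left for 15% losses, looked too good.

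Power tells readers how to interpret a non-significant result. At 80% the trial would miss its planned effect one time in five. At 64% it would miss it more than one time in three. A null result from a trial described as adequately powered could then be read as stronger evidence against LVB than the design can provide.

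**Working it through.** **Inputs, all from Statistical Analysis:** n1=40, n2=20, alpha=0.05, d=0.70, two-sample t test, 15% loss in both groups. Sidedness is unstated, so both versions are run.

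**Evaluable numbers after loss:** 40 × 0.85 = 34 and 20 × 0.85 = 17, total 51.

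**Formula** (exact noncentral t, the method for the test the article names): df = n1 + n2 − 2; noncentrality = d × √(n1·n2/(n1+n2)); power = the probability that a noncentral t variable falls beyond the critical value.

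**Noncentrality:**
- 40/20: 0.70 × √(800/60) = 0.70 × 3.651 = 2.556, df 58
- 34/17: 0.70 × √(578/51) = 0.70 × 3.367 = 2.357, df 49

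**Attempt to reproduce the stated 80%:**

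| Evaluable | Test | Critical t | Power |
|---|---|---|---|
| 40/20 | two-sided 0.05 | 2.002 | 71.0% |
| 34/17 | two-sided 0.05 | 2.010 | 63.7% |
| 40/20 | one-sided 0.05 | 1.672 | 81.1% |
| 34/17 | one-sided 0.05 | 1.677 | 75.1% |

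The only row near 80% is one-sided with nobody lost. For that setting, 60 is also the smallest 2:1 total that reaches 80%. The article's figure is therefore consistent with a one-tailed calculation without a dropout allowance. This explanation is an inference, since the G*Power output is not shown. Equal allocation does not explain the figure either: 30/30, two-sided, no loss, gives 76.0%.

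**Effect detectable with 80% power, two-sided** (solved numerically): d=0.78 at 40/20 and d=0.85 at 34/17.

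**Size needed for the claim, two-sided, 2:1:** the smallest design is 50/25 = 75 evaluable (power 80.5%). Allowing for 15% loss, 75/0.85 = 88.2, so 89 randomised, or 90 (60/30) to keep the ratio exact. Even one-sided, 60 evaluable would need 60/0.85 = 70.6, so 71 randomised.

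**Possible gain from baseline adjustment:** if d=0.70 is scaled to the unadjusted SD, adjusting for a baseline with correlation r raises the effective size to 0.70/√(1−r²). At 34/17, two-sided:
- r=0.5: 0.70/0.866 = 0.808, power 76%
- r=0.6: 0.70/0.80 = 0.875, power 82%

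Reaching 80% needs r of about 0.57 at 34/17, or about 0.44 with no loss. The article gives no r.

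**The case against.** The strongest reply has three parts.

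*Sidedness is assumed.* The article gives only alpha 0.05, and a one-sided calculation with 40/20 does yield 81%. This is fair, and the 71% and 64% should always be labelled two-sided. It does not rescue the text, because the article says the 60 already covers 15% loss, and one-sided power with 51 evaluable is 75%.

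*The analysis is not a t test.* The primary end point will be analysed by MMRM, probably with baseline adjustment, since the secondary models are described as identical in form and as controlling for baseline. MMRM also uses the 6-month data of participants who leave later, so 34/17 may be pessimistic for the 6-month comparison. This stands as a qualification: the actual chance of missing d=0.70 depends on a correlation the article does not give and on how d is scaled, and it could be lower than the t test implies. It is no defence of the stated 80%, which the article attributes to a plain two-sample t test.

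*The article concedes a small sample.* The Discussion calls the 20 controls a significant constraint and warns of unstable estimates. The same paragraph nevertheless keeps the claim of adequate power for the primary end point.

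Two smaller points are also right. Design and Setting and the Discussion contain a phrase rather than a figure, so they need softening, not renumbering. And the arithmetic does not test whether 0.70 is a cautious choice of effect for DN4 or MNSI.

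**Conclusion.** The stated figure is wrong on the article's own inputs. On a two-sided t test at alpha 0.05 and d=0.70, power is 71% with all 60 evaluable and 64% with the 51 left after the planned loss, against 80% claimed. The chance of missing the planned effect is then about 36% (100% − 63.7%), not 20%. Taking alpha as one-sided gives 75% after loss, so the statement that 60 participants deliver 80% power with dropout included fails on either reading.

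The 71% and 64% assume a two-sided test and no gain from covariate adjustment. A baseline correlation of about 0.57 or more would recover 80% after loss, but no such assumption is stated. The calculation is also lenient in one respect: it treats the primary end point as a single comparison, although it is defined jointly on DN4 and MNSI at 6 and 12 months. If alpha were split to 0.025 for each scale (an assumption; the article describes no split), two-sided power would be 60% at 40/20 and 52% at 34/17.

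**What to change.** 1. **Statistical Analysis and Abstract:** state that the test is two-sided and replace the power claim. Suggested text: 'Sixty participants will be randomised (40 and 20). With 51 evaluable after 15% loss, a two-sided t test at alpha 0.05 has 64% power for d=0.70, or 80% power for d=0.85.' If a one-sided test was intended, say so and give 75% for d=0.70 after loss.
2. **Statistical Analysis:** delete the sentence saying that the 60 already accounts for dropout.
3. **Both places:** drop the word conservative for d=0.70. With 51 evaluable the design has 80% power only for an effect of 0.85.
4. **Design and Setting, and the Discussion limitations:** remove or qualify the descriptions of the control group and the primary end point as adequately powered.
5. **Optional:** if credit for baseline adjustment is wanted, state the assumed baseline correlation, its source and the SD to which d is scaled, and report the power that follows (76% at r=0.5, 82% at r=0.6, with 34/17).

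The cost is wording only, with no extra participants; the stated power becomes less favourable. The article reports three participants enrolled and no outcome data, so the correction can be made before any results are known. Keeping 80% power for d=0.70 on the t-test basis would instead mean randomising about 89 (90 at an exact 2:1), which is a change of design.

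### The primary end point is defined in three different ways, and the sample size rests on one t test tied to no scale, visit or success rule, so neither the 5% error nor the 80% power can be established

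*Protocol article*

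**What the plan says.** The protocol article describes the primary end point in several places, and they do not agree.

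- **Statistical Analysis:** one primary end point, "jointly defined as the changes in DN4 and MNSI at 6 and 12 months", analysed by a mixed model for repeated measures (MMRM). The abstract's Methods, Aim of the Study and Outcomes also give both visits.
- **Follow-Up Assessments:** the visits are meant to "capture both the primary end point at 6 months and the durability of outcomes at 12 months". Here month 12 is not primary.
- **Abstract, Objective:** the primary objective concerns small-fibre and autonomic function at 6 months. Aim of the Study and Statistical Analysis treat the measures of that construct (skin conductance, sympathetic skin response, heart rate variability, sensory thresholds) as secondary.

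The sizing sentence says that 60 randomized participants, 40 and 20, "provides 80% power (*α*=0.05) to detect a conservative between-group effect size of Cohen *d*=0.70 for the primary end point". It adds: "This target randomized sample size accounts for an anticipated 15% dropout and missing data rate across both groups". The method is a two-sample t test in G*Power. Whether alpha is one-sided or two-sided is not stated.

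The only multiplicity method in the article concerns the exploratory biomarkers, which have "multiple testing controlled by the Benjamini-Hochberg false discovery rate".

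**The concern.** Two scales at two visits give up to four treatment contrasts. The word used to combine them can mean that all must succeed, that any one suffices, or that there is one global test. These rules have different error rates and different power, and the sizing calculation corresponds to none of them when more than one contrast is involved. The conflict over month 12 changes the number of primary contrasts from four to two, and the abstract's Objective changes the construct altogether.

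This rule decides whether the trial is declared positive. Participants and surgeons are unblinded, there is no sham procedure, and DN4 is listed among the symptom scales. A choice of scale, visit or rule that is still open when data arrive would weaken any positive claim.

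**Working it through.** **Inputs from Statistical Analysis:** n = 40 and 20; alpha = 0.05; d = 0.70; 15% dropout. After dropout, 40 × 0.85 = 34 and 20 × 0.85 = 17.

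**Assumptions, because the article gives no figures:** correlation of 0 to 0.7 between scales and 0.5 to 0.7 between visits; d = 0.70 on every contrast; no gain in precision from baseline adjustment in the MMRM.

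**Step 1. The plan's own figure, for one comparison.** Power comes from the noncentral t distribution with noncentrality d × √(n1·n2/(n1+n2)).

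- 40/20: 0.70 × √(800/60) = 2.556, on 58 degrees of freedom.
- 34/17: 0.70 × √(578/51) = 2.357, on 49 degrees of freedom.

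| Test at 0.05 | 40/20 | 34/17 |
|---|---|---|
| Two-sided | 71.0% | 63.7% |
| One-sided | 81.1% | 75.1% |

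At these sizes, 80% is reached only one-sided and with no dropout, which conflicts with the statement that dropout is already included.

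**Step 2. Error if any one contrast suffices, each at two-sided 0.05.** Under independence the familywise error is 1 − 0.95⁴ = 18.5% for four contrasts and 1 − 0.95² = 9.75% for two. Simulating four correlated normal statistics and counting draws with any |Z| > 1.96 gives:

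- any of four: about 14-17%;
- either scale at month 6 only: 8-10%.

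**Step 3. Power if several contrasts are all required, each at two-sided 0.05.** Type I error is then at most 5%. Under full independence, all four gives 0.710⁴ = 25% and both scales at month 6 gives 0.710² = 50% (40/20). The same simulation, shifted by the noncentralities above and compared with the t critical value, gives:

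| All required | 40/20 | 34/17 |
|---|---|---|
| Four contrasts | 32-48% | 23-39% |
| Both scales, month 6 | 50-60% | 40-52% |

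**Step 4. How much of the shortfall comes from the joint definition.** The fall from 80% to 71% (or 64% after dropout) is present with a single two-sided test. Requiring both scales at month 6 then costs a further 71 − 60 = 11 to 71 − 50 = 21 points at 40/20, and 64 − 52 = 12 to 64 − 40 = 24 points at 34/17.

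**The case against.** A reader might infer that both the type I error and the power fail. The documents do not support that, because the two go wrong under opposite rules. If any contrast suffices, error inflates but power is high: 84-99% across 40/20 and 34/17, with correlations of 0 to 0.7 between scales and 0 to 0.8 between visits. If all are required, the error is controlled and only power suffers.

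A reader might also infer that four separate tests at 0.05 are planned. Alpha appears once, in the sizing sentence. The wording could equally mean co-primary end points with both required, or a global test, and an MMRM can yield one effect per scale across visits. The 14-17% therefore belongs to one reading and is not a stated plan.

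The strongest objection is that this is a condensed article and the analysis plan is not shown. Success rules and alpha allocation commonly sit there, so their absence here is not itself a defect, and it cannot be said that the choice will in fact be made after the data are seen. That much of the objection stands.

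It does not remove the point. The three descriptions of the primary end point conflict within the article itself. The sample size is also fixed in the article, with a stated power that does not correspond to the end point defined in the same paragraph.

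**Conclusion.** The point holds as a contradiction in stated text together with a sizing statement that does not fit the end point. Until one time point and one rule are fixed, neither 5% error nor 80% power can be claimed for the primary end point as defined.

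The size depends on the rule adopted. An any-of-four rule roughly triples the nominal error. An all-of-four rule leaves power below one half. Requiring both scales at month 6 lies between, with power of about 40-60%. These ranges rest on the assumed correlations and on d = 0.70 for every contrast. Baseline adjustment could improve them, but the article gives nothing from which to say by how much.

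The single-test figures (71%, or 64% after dropout) need no correlation assumption, only a two-sided test. They show that the 80% would be wrong even if the joint definition were dropped.

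**What to change.** Before any outcome data are seen:

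1. Name one primary time point. Month 6 fits the abstract's Objective and Follow-Up Assessments, with month 12 as secondary durability. Keeping both visits is possible, but those two places must then be corrected and the rule must cover both visits.
2. Name one decision rule for DN4 and MNSI. One option is a fixed sequence at two-sided 0.05 on the month-6 MMRM contrast, with the second scale tested only if the first is significant. Holm is another.
3. Use identical wording in the abstract (Objective and Methods), Aim of the Study, Outcomes, Follow-Up Assessments and Statistical Analysis. This includes settling whether small-fibre and autonomic function is primary or secondary.
4. Replace the 80% with the power for the chosen rule, stating sidedness and dropout. For the first test in a fixed sequence that is 64% at 34/17. For Holm, the chance that at least one scale succeeds at month 6 is about 65-77% at 34/17, with correlation 0 to 0.7 between scales.

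If 80% for a single two-sided test at 2:1 is to be kept, 75 evaluable participants are needed, or 75/0.85 = 88.2, so 89 randomized.

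The cost is moderate. The second scale and month 12 lose stand-alone primary status, the stated power becomes less favourable, and a protocol amendment is likely to be needed. The registry entry should be checked for agreement. With 3 participants enrolled and no outcome data reported, the change can still be made credibly.

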### Aim of the Study

The aim of this study is to evaluate whether LVB combined with standard of care (SOC) provides superior outcomes compared with SOC alone in patients with DPN. We hypothesize that restoration of lymphatic-venous drainage and modulation of inflammatory and oxidative pathways will enhance small-fiber and autonomic function, reduce neuropathic pain, and accelerate ulcer healing when present. To test this hypothesis, the primary outcomes—changes in DN4 and overall neuropathy burden (as measured by the Michigan Neuropathy Screening Instrument [MNSI]) scores—will be evaluated at 6 and 12 months. These outcomes are directly linked to secondary objective measures evaluating somatic and autonomic physiology, including small-fiber sudomotor function (ESC and sympathetic skin response [SSR]), cardiovascular autonomic regulation (heart rate variability [HRV]), thermal and vibratory thresholds (QST), and large-fiber electrodiagnostics (nerve conduction studies [NCSs]). In participants with ulcers, the impact on wound repair will be examined through time to complete epithelialization, healing rates, and complication profiles. Mechanistic insights will be explored through biomarkers of oxidative stress, immune modulation, and intraepidermal nerve fiber density (IENFD), while safety assessments will ensure the tolerability of the intervention.

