Diabetic autonomic neuropathy is a key factor in the development and poor healing of diabetic foot ulcers. Assessments such as HRV and SSR are essential for evaluating this condition. A decrease in HRV indicates parasympathetic dysfunction, increasing cardiovascular risk, while an absent or reduced SSR indicates sympathetic nerve failure, causing dry, cracked skin. This dual impairment—loss of protective sensation from somatic neuropathy and compromised skin integrity from autonomic dysfunction—creates a cycle in which minor injuries go unnoticed, and the body’s natural healing processes are hindered, leading to chronic, nonhealing ulcers [27,28]. Therefore, a comprehensive assessment of both somatic and autonomic neuropathy is vital for effective management and risk stratification in patients with diabetic foot ulcers. We will evaluate the effectiveness of LVB in alleviating diabetic autonomic neuropathy.

The strengths of this study include its randomized, assessor-blinded design, the incorporation of objective autonomic and electrophysiologic end points, and the integration of biomarker and histological substudies to provide mechanistic insight. The inclusion of ulcer-related outcomes further enhances the clinical relevance of the study, as foot ulcers remain a major cause of morbidity and amputation in DPN. Positive findings, particularly improvements in small-fiber function and ulcer healing, could inform future treatment algorithms tailored to specific DPN phenotypes, thereby advancing precision care in diabetic neuropathy.

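### If the sympathetic skin response (SSR) is analysed as latency, an absent response has no value, so a missing-at-random MMRM loses the worst-affected participants and probably dilutes any benefit of lymphovenous bypass (LVB)

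*Protocol article*

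**What the plan says.** In the protocol article, Aim of the Study pairs SSR with electrochemical skin conductance (ESC) as a secondary measure of sudomotor function. Statistical Analysis then fixes the model: "Continuous secondary end points, including ESC values, SSR latencies or amplitudes, HRV parameters, and QST thresholds, will be analyzed using identical, parallel MMRM frameworks". The rest of that sentence says these models control for baseline values.

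The same section sets the missing-data rule for the trial: "Missing data will be assumed to be missing at random, with MMRM inherently accommodating missingness". The only sensitivity analysis it names for missing data is "multiple imputation using Multiple Imputation by Chained Equations applied for sensitivity analyses". It also states: "An anticipated dropout and missing data rate of 15% is expected across both groups". No separate rate is given for absent SSRs.

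The Discussion says that "an absent or reduced SSR indicates sympathetic nerve failure", and adds: "We will evaluate the effectiveness of LVB in alleviating diabetic autonomic neuropathy".

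The article does not say what value, rank or category an absent SSR receives.

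**The concern.** The sentence offers two measures as if they were interchangeable, and they behave differently when there is no response. Amplitude has a natural value, zero. Latency has none.

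Under the latency option:

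- Whether a value exists depends on the function the end point is meant to measure. That is not missing at random, and neither MMRM nor chained-equations imputation under the same assumption repairs it.
- A participant with no response at baseline has no baseline latency to adjust for.
- A participant whose response returns after LVB enters follow-up with a newly measurable and probably long latency. A comparable control whose response stays absent contributes nothing. The groups compared are then selected after randomisation.
- Regaining or losing the response, the plainest change an SSR can show, does not enter the result.

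At stake is one of the trial's autonomic measures, in a trial that aims to show better autonomic function. The primary analysis of the neuropathic pain and neuropathy burden scores is not affected.

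**Working it through.** **Plan's own figure.** There is none for SSR. The one power statement, "A total sample size of 60 randomized participants (LVB n=40; SOC n=20) provides 80% power", concerns the primary end point and does not carry over.

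**Inputs from the article.** Allocation is 40 v 20. The model adjusts for baseline and assumes missing at random.

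**Inputs assumed.** Proportion absent at baseline p = 10% to 50%; baseline to follow-up correlation 0.7; true LVB effect 0.5 SD; no other dropout; latency and absence both driven by the same latent function.

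**Step 1: participants with a baseline latency.** This is 60 × (1 − p): 54, 48, 42 and 30 at p = 10%, 20%, 30% and 50%. It is a ceiling for any model that uses baseline latency as a covariate, however many follow-up visits are attended.

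**Step 2: what latency cannot show.** The response is absent when function falls below c = Φ⁻¹(p). At follow-up, SOC absence stays at p and LVB absence is Φ(c − 0.5). For p = 30%, c = −0.524 and Φ(−1.024) = 15%, so absence is 15% v 30%. The latency analysis does not use this difference of 15 percentage points.

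**Step 3: simulated effect on the estimate.** Baseline function is B ~ N(0,1). Follow-up is Y = 0.7B + √(1 − 0.49)·e + 0.5G, with G = 1 for LVB. ANCOVA of Y on B and G uses only those above c at both visits. The comparators keep all 60, either ranked with absent tied as worst or using amplitude with absent = 0. Runs were repeated independently (3,000 per cell where stated); ranges show the spread.

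| Absent at baseline | Usable pairs of 60 | Estimate (true 0.50) | Power, latency pairs | Power, rank | Power, amplitude |
|---|---|---|---|---|---|
| 20% | about 45 | 0.42 | 46–49% | 63–64% | about 66% |
| 30% | about 38 | 0.39 | 38% | 62–63% | about 63% |
| 50% | 25–26 | 0.34–0.35 | 21–23% | 54% | about 52% |

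At 10% absent the estimate is 0.45. At 30% absent, 34% of LVB and 41% of SOC participants have no latency pair, so the loss also differs by arm.

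**Step 4: other assumptions.** With correlation 0.6 and a true effect of 0.70 SD, the observed-latency estimate is 0.62, 0.57, 0.53, 0.49 and 0.46 at 10%, 20%, 30%, 40% and 50% absent. The share retained runs from 0.62/0.70 = 89% to 0.46/0.70 = 66%. This is close to the first model, where 0.45/0.50 = 90% and 0.35/0.50 = 70%.

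**Step 5: weaker link between latency and severity.** Under the first model with 30% absent, the estimate is 0.39 if latency tracks severity perfectly, 0.43 at correlation 0.7, 0.44 at 0.5 and 0.47 at 0.3. At 10% absent and correlation 0.5 it is 0.47.

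**Step 6: no true effect.** The estimates stay near 0, and one-sided rejection is about 0.025 to 0.03 for both the latency and the rank analysis.

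**The case against.** A reader might infer that the protocol has committed to latency, that it codes an absent response as missing, and that it will impute it. The text does not go that far. It says latencies or amplitudes, and amplitude with absent = 0 keeps every participant. The missing-at-random sentence is general and is followed by the ordinary dropout allowance. How an absent response is coded is often left to an analysis plan, which is not shown. So the problem is conditional on latency being chosen.

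What remains is that the article does more than stay silent. It names latency as an acceptable continuous end point, assigns it a baseline-adjusted MMRM, and gives one missing-data assumption for everything. An analysis plan that follows the latency option inherits the difficulty.

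Three further objections limit the size. The absence rate and the link between latency and severity are assumed. The simulation is a single-visit ANCOVA on complete pairs, whereas the planned MMRM covers 6 and 12 months and can use either follow-up value; the pair counts and power figures are therefore not the protocol's own. SSR is also one of several secondary measures, ESC covers sudomotor function separately, and the article already concedes low power for smaller effects on secondary outcomes.

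Finally, SSR is missing from Outcomes, Table 1, and the baseline and follow-up assessment lists. On those lists no SSR data would be collected. That needs reconciling too, but it does not make latency a suitable end point.

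**Conclusion.** The point holds for the latency option. An absent SSR has no latency, the Discussion treats absence as a sign of nerve failure, and the stated model and missing-data assumption do not suit that situation. The probable consequence is an understated LVB effect and fewer usable participants: about 0.45 to 0.35 SD in place of 0.5 SD for 10% to 50% absent. These figures assume that latency tracks severity perfectly and use a complete-pair ANCOVA. With a weaker link the dilution is smaller, and at a low absence rate it may be slight. The loss of participants remains in either case and grows with the absence rate.

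Two stronger readings are not supported. The first is that the analysis would produce a false-positive result: with no true effect, the simulations showed no bias. The second is that the same criticism reaches the nerve conduction measures: Table 1 schedules those at baseline only, and the sentence at issue does not name them.

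This is a worthwhile correction to a secondary end point and leaves the primary analysis untouched.

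**What to change.** In Statistical Analysis, replace the either-or SSR wording with one measure and one rule:

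- Analyse SSR amplitude with an absent response scored as 0, or use a baseline-adjusted rank score with absent as the worst value.
- Report the proportion with a present SSR by arm at each visit.
- Keep latency as a descriptive summary among participants with a response.
- State that an absent response is an observed result, not missing data, and is not imputed. Reserve the missing-at-random assumption and imputation for tests that were not done.

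Then reconcile SSR with Outcomes, Table 1, Baseline Assessments and Follow-Up Assessments, so that they and the analysis list agree on whether and when it is measured.

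The analysis change is wording only and needs no extra participants. The cost is zero-heavy amplitude data, or a rank effect that is harder to read than milliseconds. The article reports 3 participants enrolled and no outcome data, so the choice can still be made before results could influence it.
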